### Participants and recruitment

Participants will be recruited from the Eating Disorder Center of the Hospital of Padova, Italy. All eligible female patients followed at the center will be invited to take part in the study, as an adjunct to TAU, in agreement with their treating clinician. Recruitment will be limited to female patients due to the low number of male patients accessing the center and to minimize potential gender-related confounding factors.

Inclusion criteria will be: (1) current diagnosis of AN according to DSM-5 criteria; (2) age ≥18 years; (3) unsuccessful completion of at least one 3-month course of outpatient treatment; (4) illness duration of at least 1 year, and (5) female gender.

Exclusion criteria will be: (1) Presence of significant neurological comorbidities or severe/unstable systemic diseases, (2) Diastolic blood pressure < 60 mmHg or heart rate < 60 bpm, (3) diagnosis of psychosis or substance abuse disorders, (4) history of hypomanic/manic episodes, (5) Current suicidal ideation, (6) known contraindications to TMS as assessed with the TMS safety checklist (Rossi et al., 2021), including epilepsy, head trauma with loss of consciousness, severe/frequent headaches, cochlear implants, pacemakers, pregnancy, metallic implants, implanted neurostimulators; and (7) known contraindications to MRI, as assessed with the Hospital of Padova MRI safety checklist (Mod. Rev. 2, 16/05/2023), including presence of medical devices or metallic material, history of surgery or significant physical trauma, claustrophobia, pregnancy.

*A priori* power analysis conducted with G^*^Power (Faul et al., 2007) indicated that 28 participants are required to detect a significant group (2) × time (3) interaction assuming a medium effect size (Cohen's *f* = 0.25), statistical power of 1–β = 0.80, and significance level α = 0.05, with a correlation among repeated measures of *r* = 0.5. To account for potential dropouts, the sample size will be increased by 20%, resulting in a final target enrollment of 34 participants.

The study has been approved by the Ethics Committee of the Hospital of Padova (protocol number 6168/EST/25) and registered on ClinicalTrials.gov (registration number: NCT07106645). Written informed consent will be obtained from all participants prior to enrollment. Participants will be informed that their involvement is voluntary and that they may withdraw at any time without any consequences for their ongoing treatment.

### Intervention

#### Treatment as usual

In this study, iTBS is delivered as an add-on to treatment as usual (TAU) provided by a specialized eating-disorder service. TAU reflects a guideline-consistent, multidisciplinary and coordinated care pathway, and may include: (1) nutritional rehabilitation with dietetic assessment and monitoring, (2) regular medical monitoring of physical status and risk parameters, (3) eating-disorder-focused psychological support/psychotherapy, (4) psychoeducation, and (5) when indicated, family involvement/support. Pharmacological treatment may be part of TAU when clinically indicated. To reduce TAU-related confounding, the type and intensity of TAU will be kept as stable as clinically feasible during the 4-week stimulation period; any changes in treatment setting/intensity or medication will be prospectively documented. TAU intensity variables (e.g., outpatient vs. day-hospital setting, frequency of clinical/psychological/dietetic contacts, and medication changes) will be monitored throughout the study and considered in sensitivity analyses (and as covariates where appropriate).

#### Randomization and blinding procedure

Randomization will be implemented using patient codes provided by the coil manufacturer. The randomization procedure relies on the certified double-blind system integrated in the MagVenture MagPro platform for sham-controlled rTMS studies. Each participant will be assigned a unique code, corresponding to a pre-generated allocation to active or sham stimulation, which is entered into the TMS device at the beginning of each session. Participant codes are assigned at enrollment by a study member not involved in outcome assessments. Based on this code, the device automatically recognizes whether the participant receives real or sham stimulation, without revealing the stimulation condition to the operator or the participant. The coil is designed with two indistinguishable sides (active and sham), and the system instructs the operator only on whether the coil is in the correct position or needs to be rotated. Thus, the operator is aware only of coil positioning but remains blind to the actual stimulation condition. The randomization sequence is generated and managed externally to the study team through the device-coded procedure, ensuring full allocation concealment. Both participants and study personnel involved in treatment administration are therefore kept blinded to allocation, ensuring a double-blind design. At the end of the treatment, both participants and the operators who administered the stimulation will be asked to guess whether the participant received active or sham stimulation, as a measure of blinding integrity.

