**Methods:**

Thirty-four adults with AN (≥18 years, illness ≥12 months, ≥1 prior unsuccessful treatment) will be randomized (1:1) to 20 sessions of real or sham iTBS over 4 weeks. Stimulation will be delivered with a MagPro system and a Cool B70 A/P active/sham coil; motor threshold will be estimated with the Stochastic Approximator (SAMT) and re-checked weekly. Individualized stimulation target will be defined based on resting state functional magnetic resonance imaging data to identify the cortical region within the PPC that is maximally functionally connected with the activity of two meta-analytically derived networks representing body representation and implicit behavioral tendencies. Coil placement will be neuronavigated on individual T1 magnetic resonance imaging (MRI). Assessments will take place at baseline (T0), post-treatment (T1), and 4-month follow-up (T2), covering clinical status (body mass index (BMI), psychopathology, and quality of life), experimental tasks (implicit body representation, peripersonal space, approach–avoidance tendencies toward food, interoceptive accuracy, and neurocognitive functioning), and MRI. Feasibility endpoints include recruitment, retention, completion, blinding, and tolerability. Ethics approval: 6168/EST/25; registration: NCT07106645.

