#### Stimulation sessions

TMS will be delivered using a MagPro stimulator (MagVenture, Denmark) equipped with a Cool B70 A/P coil, which allows for active stimulation on one side and integrated sham functionality on the opposite side, ensuring a reliable double-sham protocol.

The procedure and stimulation will be identical for participants in both the active and control groups, with the only difference being that in the sham condition the coil is oriented so as not to stimulate the brain, as described above.

All participants will receive 20 sessions of TMS over 20 consecutive weekdays. Except for the first session, which will be longer due to the requirements of neuronavigation, the remaining sessions are expected to last approximately 20–30 min, including preparation time, 3 min of stimulation, and debriefing. The stimulation protocol will follow a standard iTBS paradigm, consisting of bursts of three pulses at 50 Hz, repeated at 5 Hz for a total duration of 3 min, delivered at 100% of the participant's resting motor threshold (Huang et al., 2011). This temporal pattern was selected for its documented capacity to induce durable, plasticity-like modulation of cortical excitability, in line with established theta-burst stimulation frameworks, and not to directly entrain region-specific theta oscillations.

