#### Safety monitoring and side effects

All study procedures and stimulation parameters will follow the most recent international safety and application guidelines for TMS (Rossi et al., 2021). For each participant, a case report form will be maintained to document session attendance, protocol adherence, and the occurrence of any side effects or adverse events based on predefined criteria. Minor adverse effects (e.g., transient headache) will not necessitate withdrawal from the study, although participants will retain the right to discontinue treatment at any time. In contrast, TMS will be immediately interrupted if a serious adverse event occurs (e.g., an epileptic seizure). After the first and the last stimulation session, participants will also complete the TMSens_Q, a standardized questionnaire designed to record any sensations or adverse effects experienced during or after TMS, in order to systematically monitor tolerability and safety (Giustiniani et al., 2022). In addition to minor side effects, potential longer-lasting effects on visuospatial attention due to PPC stimulation will be monitored with pre- and post-stimulation neurocognitive assessment.

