Fourth, methodological risks also warrant consideration. Achieving a convincing sham condition remains challenging in TMS trials, even with the use of advanced double-coil systems, as subtle differences in scalp sensations or auditory cues may compromise blinding (Duecker and Sack, 2015), with potential resentful demoralization that could jeopardize compliance, or compensatory rivalry that could hinder the detection of treatment effects (McCambridge et al., 2014). Moreover, the mere possibility of being randomized to the sham arm can reduce willingness to participate and heighten concerns about the treatment, particularly in a population where ambivalence toward intervention is already common. For these reasons, assessing blinding integrity and carefully documenting reasons for refusal or discontinuation will be crucial for interpreting trial outcomes and for informing the design of future studies.

In summary, this protocol combines a neurobiologically informed stimulation strategy with outcome measures that capture both explicit and implicit dimensions of AN, while addressing the practical and methodological challenges inherent to this population. The findings are expected to inform not only the feasibility of posterior parietal non-invasive stimulation in treating AN, but also its potential role within the broader landscape of precision interventions for eating disorders.

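### The only allocation guess is taken after the 4-week course, so above-chance guessing could not be attributed to the sham rather than to perceived benefit

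*Protocol article*

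**What the plan says.** The protocol article, under Randomization and blinding procedure, sets one guess: "At the end of the treatment, both participants and the operators who administered the stimulation will be asked to guess" whether stimulation was active or sham, "as a measure of blinding integrity". The guess follows a full course: "All participants will receive 20 sessions of TMS over 20 consecutive weekdays" (Stimulation sessions).

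The result carries weight. The Abstract states: "Feasibility endpoints include recruitment, retention, completion, blinding, and tolerability". The Discussion gives the reason for concern, that "subtle differences in scalp sensations or auditory cues may compromise blinding", and adds that "assessing blinding integrity and carefully documenting reasons for refusal or discontinuation will be crucial for interpreting trial outcomes".

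Sensations are recorded earlier than the guess. Under Safety monitoring and side effects: "After the first and the last stimulation session, participants will also complete the TMSens_Q". That questionnaire is assigned to tolerability and safety, is completed by participants only, and is not described as including an allocation guess.

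The Introduction predicts a larger BMI gain and a larger fall in psychopathology in the active arm. The article does not say whether a participant who stops early is asked to guess at that point.

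**The concern.** The named threat is sensory and can be present from the first session. The guess comes four weeks later, when participants also know how they have fared and operators have met them at each session. A correct guess can then have two sources: the coil felt or sounded different, or the patient improved (or did not) and reasoned back to the allocation. Only the first is a fault of the sham.

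The two sources are hardest to separate when the trial's own hypothesis is true. An adequate sham could then look as if it had failed, in a feasibility study meant to guide a confirmatory trial. Analysis cannot repair this later, because an early guess that was never collected cannot be recovered.

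**Working it through.** The plan gives no figure for the blinding endpoint, so there is none to reproduce. The arm size used below is 34/2 = 17. The 34 itself checks out: the stated inputs (f = 0.25, r = 0.5, alpha 0.05, two groups, three times) give power 0.812 at N = 28, and 28 × 1.2 = 33.6, rounded up to 34. The point does not depend on that calculation.

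**Step 1. Perfect sham, guessing from clinical course.** Assumptions, none from the documents: improvement is normal in each arm with a between-arm difference of d SD. A share w of patients guess active if their improvement exceeds the midpoint between arms. The rest guess 50:50. Then

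P(correct) = w·Φ(d/2) + (1 − w)·0.5, and the Bang index in each arm = 2·P(correct) − 1.

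| d | w = 1: correct (Bang) | w = 0.5: correct (Bang) |
|---|---|---|
| 0 | 50% (0) | 50% (0) |
| 0.25 | 55.0% (0.099) | 52.5% (0.050) |
| 0.5 | 59.9% (0.197) | 54.9% (0.099) |
| 0.8 | 65.5% (0.311) | 57.8% (0.155) |
| 1.0 | 69.1% (0.383) | 59.6% (0.191) |

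**Step 2. Leaking sham, no clinical effect.** Let a share s of patients in each arm recognise their condition by sensation or sound and the rest guess 50:50. Then P(correct) = s + (1 − s)/2, and the Bang index = 2·[s + (1 − s)/2] − 1 = s in both arms. A leak reaching 19.7% of patients therefore gives exactly the result of a perfect sham with d = 0.5 and w = 1. A leak of 31.1% matches d = 0.8 and w = 1. The end guess alone cannot tell these apart.

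**Step 3. A less symmetric model.** Let a share q of an arm feel better. Patients who feel better guess active with probability p1, the others with p0, so P(guess active) = q·p1 + (1 − q)·p0. The sham is again perfect and all inputs are assumed.

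- p1 = 0.8, p0 = 0.4, q = 0.6 (active) and 0.3 (sham): 0.48 + 0.16 = 0.64 and 0.24 + 0.28 = 0.52. Correct (0.64 + 0.48)/2 = 56%. Bang 0.28 (active), −0.04 (sham).
- p1 = 0.9, p0 = 0.3, q = 0.7 and 0.2: 0.63 + 0.09 = 0.72 and 0.18 + 0.24 = 0.42. Correct 65%. Bang 0.44 and 0.16.
- p1 = 0.7, p0 = 0.45, q = 0.5 and 0.35: 0.575 and 0.5375. Correct (0.575 + 0.4625)/2 = 51.9%. Bang 0.15 and −0.075.

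In the first and third cases the active-arm index partly reflects a general lean towards guessing active. The gap between arms (12 points, then 3.75 points) is the better measure.

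**Step 4. Precision.** At chance, the 95% half-width of one arm's Bang index is 2 × 1.96 × √(0.25/n): 0.48 at n = 17 and 0.52 at n = 14.

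**Step 5. If early stoppers were not asked.** Suppose 3 of 17 sham patients give no guess and 7 of 14 completers guess sham. Over all 17 the share guessing sham could lie between 7/17 = 41% and 10/17 = 59%, a Bang index from −0.18 to +0.18.

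**The case against.** A reader might infer that an end-of-course guess cannot show whether the sham works. The documents do not support that. The distortion needs both a between-arm difference in perceived benefit and guessing based on it. At d = 0 it vanishes, and a near-chance result would still be evidence for the sham. Reporting by arm also helps in part, since a lean towards guessing active (0.28 and −0.04) looks different from a leak that raises both arms. It does not help in the symmetric case of steps 1 and 2.

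The session-1 TMSens_Q already allows sensations to be compared between arms before any clinical course. That stands as partial evidence. It does not show whether anyone drew a conclusion about allocation, and it does not cover operators.

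A reader might also infer that early stoppers are left out, and that the drop-out allowance (34 − 28 = 6 of 34) gives the number lost. Neither is stated. The end of treatment may include an early end, and a condensed article may leave this to the full protocol. The allowance serves an analysis running to the 4-month follow-up, so 6 is at most an upper bound: anyone lost after the course would already have guessed.

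The case for operators is weaker than for patients. Weight, eating behaviour and mood are recorded by an independent psychiatrist, and nothing says operators see those records.

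The shifts are also small against the noise: every arm-level Bang value above is below the half-width of 0.48. That is fair, and a session-1 guess would be equally imprecise. It would, however, be free of influence from the later clinical course.

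**Conclusion.** The point holds in a limited form. With the guess taken only at the end, an above-chance result cannot be attributed to the sham if the arms differ in perceived benefit, which is what the trial predicts. Under the assumed models, a perfect sham with a benefit of 0.5 to 0.8 SD gives 54.9% to 65.5% correct guesses, depending on how many patients guess from their course. A sensory leak can produce the same figures. A near-chance result would remain informative.

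This is an avoidable weakness in a stated endpoint. It is not a contradiction, and it affects neither the sample size nor the efficacy analysis. The size rests on assumed guessing behaviour; the direction rests on the stated timing and the trial's own hypothesis. If the full protocol already collects an earlier guess, the point falls away.

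**What to change.** - Right after session 1, alongside the TMSens_Q already given then, ask participant and operator for a guess, with confidence and main reason.
- Keep the end-of-treatment guess as a co-reported reading and do not demote it. Unblinding can build over 20 sessions, and blinding at the post-treatment assessment protects the self-report outcomes.
- State that a participant who stops early is asked for the guess and the TMSens_Q at the last session received, and that the operator's guess is taken then too.
- Report both time points by arm, with confidence intervals, and read the early guess together with the session-1 TMSens_Q.

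The cost is a few questions at a contact that already takes place, with no change to visits, treatment or sample size. The downside is small: an early question may draw attention to allocation. With about 17 per arm, neither guess will be precise.

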#### Motor threshold determination

Based on the participant's T1-weighted structural MRI, the Localite TMS Navigator system will be used to position the coil over the primary motor cortex (M1). Resting motor threshold (MT) will be determined using the SAMT (Stochastic Approximator of Motor Threshold) method, an adaptive algorithm designed to estimate MT efficiently and accurately. SAMT employs a digital control sequence with harmonic step adjustments, typically requiring around 20 pulses and achieving a median relative error of less than 1.5% (Wang and Peterchev, 2023; Wang et al., 2025). Electromyographic (EMG) recordings will be obtained from the first dorsal interosseous muscle to measure motor-evoked potentials (MEPs). At the beginning of the procedure, the operator will enter an initial stimulation intensity into the SAMT program. After each TMS pulse, the operator indicates whether a motor response has occurred—defined as an MEP of ≥50 μV. Based on this input, SAMT automatically adjusts the stimulation intensity for the next pulse, iteratively converging on the participant's MT in a controlled and efficient manner. To ensure safety and efficacy, the MT will be assessed weekly for each participant.

#### Localization of the stimulation target

The precise stimulation target will be individualized for each participant based on resting-state functional connectivity, with the aim of identifying the posterior parietal node showing the strongest connectivity with networks involved in implicit behavioral tendencies and body representation. These networks have been defined through a meta-analysis conducted using the Neurosynth platform (Kent et al., 2026), employing the following search terms: (1) “affordance” OR “habit” OR “motor program” and (2) “body representation” OR “body schema” OR “peripersonal” OR “multisensory integration” OR “embodiment.” In more detail, the Neurosynth-derived maps have been first thresholded to retain only the voxels with assigned values >2 standard deviations, hence ensuring that only regions that have been consistently reported across studies wilinl be retained. To further define a more precise target, the thresholded maps related to *behavioral tendencies-* and *body*- specific activations have been merged, binarized and only the voxels in overlap have been used to define the final target. The resulting Neurosynth-derived network primarily involved left-lateralized sensorimotor and parietal regions, with additional contributions from frontal, occipital and temporal cortices. Specifically, spatial overlap with the AAL3 atlas indicated involvement of the left precentral and postcentral gyri, bilateral supplementary motor area, left superior and inferior parietal lobules, left superior frontal gyrus, left middle occipital cortex, and left middle temporal gyrus (see Supplementary Table S1 for voxel-wise overlap). This resultant map will be co-registered to the individual functional neuroimaging space and used to extract its average blood oxygen level dependent (BOLD) signal over time (i.e., for the entirety of the functional neuroimaging scan acquisition). Next, we will define a search space consisting of 37 bilateral posterior parietal regions derived from the Schaefer 200 parcels atlas (Schaefer et al., 2018), which will also be coregistered to the individual functional neuroimaging space (for more details, see MRI protocol section). The individualized TMS target will be chosen as the region that is maximally functionally connected with the networks' overlap map based on the Pearson's correlation between their timeseries. To ensure biological meaningfulness and consistency of individualized targeting, only regions showing at least moderate functional connectivity with the overlap network will be considered eligible targets (*r* > 0.30). Of note, in consideration of the fact that the TMS pulse cannot reach deep cortical structures, no medial regions will be considered in the search space. The methodological overflow is depicted in Figure 1.

**Figure 1 F1:**
[figure not shown]
Graphical overview of the neuroimaging protocol for individualized TMS target selection.

Once the individual TMS target is identified, its Montreal Neurological Institute (standard space/template) (MNI) coordinates will be communicated to the researcher in charge of delivering the stimulation, which will happen within a week from the neuroimaging acquisition. At the time of stimulation, coil positioning on the scalp will then be guided using the Localite TMS Navigator system, based on the participant's T1-weighted structural MRI and three skull landmarks (inion and the outer canthi of both eyes), allowing accurate placement of the coil over the individualized target. The coil position will subsequently be marked on the participant's cap, so that the full localization procedure needs to be performed only during the first session.

#### Stimulation sessions

TMS will be delivered using a MagPro stimulator (MagVenture, Denmark) equipped with a Cool B70 A/P coil, which allows for active stimulation on one side and integrated sham functionality on the opposite side, ensuring a reliable double-sham protocol.

The procedure and stimulation will be identical for participants in both the active and control groups, with the only difference being that in the sham condition the coil is oriented so as not to stimulate the brain, as described above.

All participants will receive 20 sessions of TMS over 20 consecutive weekdays. Except for the first session, which will be longer due to the requirements of neuronavigation, the remaining sessions are expected to last approximately 20–30 min, including preparation time, 3 min of stimulation, and debriefing. The stimulation protocol will follow a standard iTBS paradigm, consisting of bursts of three pulses at 50 Hz, repeated at 5 Hz for a total duration of 3 min, delivered at 100% of the participant's resting motor threshold (Huang et al., 2011). This temporal pattern was selected for its documented capacity to induce durable, plasticity-like modulation of cortical excitability, in line with established theta-burst stimulation frameworks, and not to directly entrain region-specific theta oscillations.

